2.4.5.2 Secondary Outcomes

**2.4.5.2.1Constipation Symptom and Efficacy Assessment Scale (CSEAS)**

The Constipation Symptom and Efficacy Assessment Scale (CSEAS) is used to assess the improvement of the patient's symptoms and the efficacy of treatments in patients with constipation. It consists of six dimensions, including Difficulty, Bristol, Time, Incompleteness, Frequency, and Bloating. The score for each dimension ranges from 0 to 3 points. The total score ranges from 0 to 18, with higher scores indicating more severe constipation. Table S2 depicts details of the CSEAS. The CSEAS will be evaluated at baseline, post-treatment, and at follow-up.

**Table S2. Details of the Constipation Symptom and Efficacy Assessment Scale (CSEAS)**

| Score | Difficulty: painful evacuation effort | Bristol:  the stool properties criteria | Time: munities in lavatory per attempt (min) | Completeness: feeling incomplete evacuation | Frequency (days/time) | Bloating: abdominal distention |
| --- | --- | --- | --- | --- | --- | --- |
| 0 | Never | 7~4 | ＜10 | Never | 1~2 | Never |
| 1 | Rarely | 3 | 10~15 | Rarely | 3 | Rarely |
| 2 | Sometimes | 2 | 15~25 | Sometimes | 4~5 | Sometimes |
| 3 | Always | 1 | ＞25 | Always | ＞5 | Always |

**2.4.5.2.2 Patient-Assessment of Constipation Quality of Life (PAC-QOL)**

The PAC-QOL is used to assess the quality of life of patients with constipation and consists of 28 items with 4 dimensions: physical discomfort, psychosocial discomfort, satisfaction, and worriedness and concerns. Each item's score ranges from 0 to 4. The total score ranges from 0 to 112, with lower scores indicating better quality of life in patients with constipation. The PAC-QOL will be rated at baseline, post-treatment, and follow-up.

**2.4.5.2.3 Unified Parkinson's Disease Rating Scale (UPDRS)**

The UPDRS is a common scale used to assess the general condition of PD patients, mainly focusing on motor symptoms, activities of daily living ability, degree of disease progression, post-treatment status, side effects of treatment and complications of PD patients. The UPDRS consists of four dimensions: the UPDRS I is used to assess the mental, behavioral, and emotional symptoms; the UPDRS II is used to assess the ability of daily living; the UPDRS III is used to assess the motor signs of PD patients; and the UPDRS IV is used to assess the comorbidity. The UPDRS will be assessed at baseline, post-treatment, and follow-up.

2.4.5.3 Evaluation of blinding effects

At the end of the trial, we will ask patients to guess their assignment status and whether they think the acupuncture needle entered the skin in order to evaluate the impact of blinding.

3. Safety Assessment

The vital signs of the patients will be recorded before and after the treatment, and the occurrence of acupuncture-related adverse effects, such as needle dizziness, needle bending, needle stagnation, needle breakage, bleeding, and subcutaneous hematoma, will be described in detail during the treatment. In the event of any adverse event caused by acupuncture, it will be promptly treated, and recorded in the "Adverse Event Record Form" of the case observation form. In the event of serious adverse events, acupuncture treatment will be discontinued immediately, and the record and treatment will be in accordance with the standards and reported to the Ethics Committee of the First Affiliated Hospital of Guangzhou University of Chinese Medicine. After obtaining the patient's wish, the physician will determine whether the patient is still suitable for study participation.

4. Interventions

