2.3 Study Objectives

We designed a randomized controlled clinical trial to compare the efficacy and safety of manual acupuncture (MA) to sham acupuncture (SA) in the treatment of PDC.

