2.4.1.3 Blinding

This study will be blinded to patients, outcome assessors, and statisticians. The treatment time for patients in different groups will be set at different times of the day to prevent communication between the two groups. During the treatment, the patients will be required to wear an eye mask to ensure the implementation of the blinding method. All operations will be performed according to a standardized procedure to ensure consistency of operation. The efficacy assessor will not be involved in the grouping and treatment manipulation. The blinding will be removed at the end of the treatment, and patients will be informed of their grouping after treatment as well as will be told their type of acupuncture after follow-up.

This study will be controlled using a special acupuncture device which was developed and designed by our team members. The special acupuncture device was shown in Supplementary Figure S2. The acupuncture device consisted of a base, a cannula, and a specially designed acupuncture needle. There are classified into two types of bases. In the MA group, the base has a longitudinal opening at the bottom, through which acupuncture needles can be pierced into the skin. Conversely, the SA group's base has a closed adhesive with no opening at the bottom, so special flat-head needling can contact the skin through the adhesive but cannot pierce it. The cannula is removable and can be adjusted to meet the needs of various needling angles depending on the site of needling. The special flat-head needle has the same shank as ordinary acupuncture needle. Since the flat-head needle do not actually pierce the skin, it is designed to be shorter in length than ordinary acupuncture needle, and the length of the body exposed during needling is the same as that of ordinary acupuncture needle to ensure consistency of appearance during operation.

The special acupuncture device to be used in this study has been approved for a national utility model patent, with the patent number ZL202121352221.7 and is produced by a manufacturer with relevant qualifications (Guangzhou Suixin Medical Equipment Co., Ltd.). The related article has been published(Wang et al., 2022).

[figure not shown]

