**Supplementary Figure S3. Trial flow chart**

**Table S1. Time of visit and data collection**

|  | **Baseline** | **Allocation** | **Treatment** | | | | | **Follow-up** | |
| --- | --- | --- | --- | --- | --- | --- | --- | --- | --- |
| Time point (Week) | -1 | 0 | 1 | 2 | | 3 | 4 | 8 |  |
| **Enrollment** |  | | | |  |  |  |  |  |
| Signing consent | **×** |  |  |  | |  |  |  |  |
| Screening | **×** |  |  |  | |  |  |  |  |
| Dose of levodopa | **×** |  |  |  | |  |  |  |  |
| Randomization |  | **×** |  |  | |  |  |  |  |
| **Interventions** |  | | | |  |  |  |  |  |
| Manual acupuncture group |  |  | **×** | **×** | | **×** | **×** |  |  |
| Sham acupuncture group |  |  | **×** | **×** | | **×** | **×** |  |  |
| **Assessments** |  | | | |  |  |  |  |  |
| Weekly CSBMs | **×** | **×** | **×** | **×** | | **×** | **×** | **×** |  |
| CSEAS |  | **×** |  |  | |  | **×** | **×** |  |
| PAC-QOL |  | **×** |  |  | |  | **×** | **×** |  |
| UPDRS |  | **×** |  |  | |  | **×** | **×** |  |
| Assessment of blinding |  | **×** |  |  | |  |  | **×** |  |
| Adverse events |  |  | **×** | **×** | | **×** | **×** |  |  |

Weekly CSBMs= weekly complete spontaneous bowel movements; CSEAS=Constipation Symptom and Efficacy Assessment Scale; PAC-QOL= Patient-Assessment of Constipation Quality of Life questionnaire; UPDRS= Unified Parkinson’s Disease Rating Scale.

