2.4.5 Outcomes Measurements

2.4.5.1 Primary Outcome

**2.4.5.1.1** **The change of weekly complete spontaneous bowel movements (CSBMs).**

We use weekly CSBMs to observe changes in the number of bowel movements in patients with constipation. CSBMs are defined as the number of bowel movements that have occurred in the past 24 hours without the use of emergency medication. CSBMs are recorded by patients on an electronic bowel diary under the direction of an independent outcome assessor. Weekly CSBMs will be collected at baseline (week 0), post-treatment (week 4), and follow-up (week 8), and differences from baseline levels are compared at weeks 4 and 8.

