4.4 Emergency treatment

When patients don`t have bowel movements for more than three consecutive days or experience intolerable symptoms such as bloating due to constipation, they are allowed to use emergency medications under medical supervision with detailed documentation. The emergency treatment consisted of lactulose and glycerin enemas. Lactulose will be used for patients who do not have bowel movements, and glycerin enemas will be used for patients who strain during defecation. The specifications of the emergency medications are as follows: Lactulose Oral Liquid (Hunan Keren Pharmaceutical Company, Approval No.: State Pharmaceutical Code H20093523), 15 ml per dose at 12-hour intervals, 2 doses in total; Glycerin Enemas (Guangdong Hengjian Pharmaceutical Company, Approval No.: H44023815), 1 stick each time in total.

5. Statistical analysis and processing

SPSS 26.0 will be used as the statistical analysis software for this study. We used the intention-to-treat (ITT) principle, regardless of whether the patients completed all assigned intervention sessions. Continuous variables were expressed as mean (SD) or median (IQR); independent t-tests were used for normally distributed values, and Mann-Whitney U tests were used for skewed data. Categorical variables were expressed as frequencies and percentages and analyzed using the χ2 or Fisher exact test, as appropriate. A repeated measures analysis of variance (ANOVA) was used to detect trends in score changes and treatment effects at different time points within groups. Multiple interpolation (MI) methods were used to estimate missing data for the primary and secondary outcomes. To assess the robustness of MI methods under the assumption of randomization, sensitivity analyses of the primary outcome were performed using per-protocol (PP) sets. Differences between groups were reported using 95% confidence intervals and bilateral P values, with values less than 0.05 considered significant.

Safety analysis: Adverse events are analyzed in all participants who received treatment, including the incidence of adverse events and the specific description of adverse events. The data are summarized as n (%). χ2 test or Fisher’s exact test is used for the comparison between treatment groups.

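### Recording of non-serious adverse events is tied to acupuncture causality and scheduled only for weeks 1 to 4, yet the planned group comparison is of all adverse events

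*Protocol*

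**What the plan says.** Safety is part of the objective: Section 2.3 sets out to "compare the efficacy and safety of manual acupuncture (MA) to sham acupuncture (SA").

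Four places govern what enters the safety data:

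- **Section 3, Safety Assessment.** During treatment, staff describe "the occurrence of acupuncture-related adverse effects, such as needle dizziness, needle bending, needle stagnation, needle breakage, bleeding, and subcutaneous hematoma". The rule for the record form follows: "In the event of any adverse event caused by acupuncture, it will be promptly treated, and recorded". The next sentence deals with serious events: "In the event of serious adverse events, acupuncture treatment will be discontinued immediately, and the record and treatment will be" according to the applicable standards, with a report to the ethics committee. That sentence carries no causality condition and no time limit.
- **Table S1.** The row is headed "Adverse events", without qualification. It is marked at weeks 1, 2, 3 and 4 and blank at week 8. Weekly CSBMs, CSEAS, PAC-QOL, UPDRS and the blinding assessment are all marked at week 8.
- **Section 5, safety analysis.** "Adverse events are analyzed in all participants who received treatment, including the incidence of adverse events". The groups are compared by a chi-square or Fisher exact test. Nothing restricts the analysis to related events.
- **Section 2.4.1.3, Blinding.** Patients, outcome assessors and statisticians are blinded; the treating physician is not listed. Under the sham device the "special flat-head needling can contact the skin through the adhesive but cannot pierce it".

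**The concern.** Section 5 plans to analyse a wider quantity than Section 3 plans to record. An analysis plan cannot repair this, because the recording rule decides which events exist in the database.

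Two kinds of non-serious event are exposed. The first is an event that nobody attributes to needling, for example a complaint after emergency lactulose or an enema, or worsening Parkinson's symptoms. The second is any event in weeks 5 to 8, when nothing is scheduled to elicit it.

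The causality condition also opens a route to bias. If the person who decides whether acupuncture caused an event knows the arm, the threshold may differ between arms, since it is harder to blame a needle that was never inserted. The protocol neither names that person nor requires the role to be blinded. What is at stake is whether the between-group safety result can be read as a comparison of harm.

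**Working it through.** **1. The passages side by side**

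| Question | Section 3 | Table S1 | Section 5 |
| --- | --- | --- | --- |
| Which non-serious events? | Those caused by acupuncture | All, by its label | All, by its wording |
| When? | Acupuncture-related effects: during treatment | Weeks 1 to 4 | No limit stated |
| Serious events? | Recorded and reported; no causality condition or time limit | Not separated | Not separated |
| Who judges cause? | Not stated | Not stated | Not stated |

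The blank at week 8 does not look like a conversion fault. The CSEAS row of the same table falls at weeks 0, 4 and 8, matching the baseline, post-treatment and follow-up times in Section 2.4.5.2.1. Section 2.4.5.1.1 confirms the week 8 assessment: "Weekly CSBMs will be collected at baseline (week 0), post-treatment (week 4), and follow-up (week 8").

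**2. Calendar coverage**

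Outcomes run to week 8, and adverse events are scheduled for weeks 1 to 4. Uncovered share = (8 − 4)/8 = 50% of post-allocation weeks.

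**3. Could attribution distort the test?**

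The protocol gives no adverse-event rates, so this part is illustrative. The only plan figure used is 39 per arm, which reproduces: 31 per group with 20% loss gives 31/0.80 = 38.75, rounded up to 39.

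Assume the same true proportion p of participants with an event in both arms. Let a be the proportion of those events attributed to acupuncture and so recorded. Then:

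- recorded rate = p × a, separately for manual acupuncture (MA) and sham (SA);
- expected recorded count = 39 × p × a;
- the probability of a Fisher exact p below 0.05 is summed over the two binomial distributions.

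Worked case: p = 20%, a = 80% in MA and 40% in SA. Recorded rates are 0.20 × 0.80 = 16% and 0.20 × 0.40 = 8%. Expected counts are 39 × 0.16 = 6.2 and 39 × 0.08 = 3.1.

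| True rate, both arms | Attributed MA / SA | Recorded MA / SA | Probability of a falsely significant difference |
| --- | --- | --- | --- |
| 10% | 50% / 50% | 5% / 5% | 0.004 |
| 10% | 80% / 40% | 8% / 4% | 0.023 |
| 10% | 90% / 10% | 9% / 1% | 0.097 |
| 20% | 50% / 50% | 10% / 10% | 0.016 |
| 20% | 80% / 40% | 16% / 8% | 0.107 |
| 20% | 90% / 10% | 18% / 2% | 0.517 |
| 30% | 50% / 50% | 15% / 15% | 0.025 |
| 30% | 80% / 40% | 24% / 12% | 0.202 |
| 30% | 90% / 10% | 27% / 3% | 0.829 |

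With equal attribution the false-positive rate stays below 5%, and the harm is loss of events: half of them at a 50% filter. A spurious difference needs attribution that differs by arm.

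**The case against.** Several stronger readings are tempting, and the protocol does not support them.

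- **That no event is recorded unless acupuncture caused it.** Section 3 does not say so. Its serious-event sentence has no causality condition, and the labels in Table S1 and Section 5 are unqualified. Section 2.4.3.3 withdraws a case after a serious or unexpected event, and Section 5 describes the causes of dropout by group. This stands. It narrows the point to non-serious events, and to a conflict between sections rather than a blanket exclusion. The dropout route helps only for events that end participation.
- **That serious events in weeks 5 to 8 go uncounted.** The serious-event sentence has no time limit; only scheduled collection stops at week 4.
- **That attribution is unblinded and the comparison therefore biased.** No section assigns the causality judgement to the treating physician. That this physician handles different devices and is not listed as blinded makes arm-dependent attribution plausible, but it remains a risk.
- **That a test on needle-specific events is meaningless because sham cannot pierce the skin.** Rarer bleeding or haematoma under sham is a real difference in harm between the two procedures, and Fisher's test copes with zeros. For 6 versus 0 at 39 per arm, two-sided p = 2 × C(39,6)/C(78,6) = 2 × 3,262,623/256,851,595 = 0.025.

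The sponsor may add that all 12 sessions fall in weeks 1 to 4 and the named harms are procedural, so few events may arise later. That is fair: 50% is a share of calendar time and does not measure missed harm.

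**Conclusion.** The point holds in a limited form. Followed as written, Section 3 and Table S1 would supply a causality-filtered set of non-serious events, collected on schedule for 4 of 8 weeks, to a Section 5 analysis that claims all adverse events. The mismatch and the missing week 8 collection can be read directly from the protocol. Loss of non-attributed or late non-serious events is a likely consequence, but its size is unknown.

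Bias between arms is conditional on attribution differing by arm. Under the assumed rates and an 80%/40% split, the chance of a falsely significant result runs from 0.023 to 0.202. It goes higher only under the extreme 90%/10% split. These figures rest on assumed rates and filters and on one recorded outcome per participant. They show the mechanism and do not estimate what this trial would see. The change should be made, but the point does not touch the primary efficacy analysis or the sample size.

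**What to change.** Reconcile Section 3, Table S1 and the safety paragraph of Section 5:

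1. Record every adverse event regardless of cause, elicited by the same open question in both arms.
2. Make relatedness a separate field on the form. State who judges it and whether that role is blinded.
3. Add adverse events to the existing week 8 assessment in Table S1. If this is not done, limit the safety conclusion to the treatment period.
4. Compare all-cause events between groups, and also report needle-specific events separately.

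The cost is a change to the case form, one table cell and a few more events to record; the week 8 assessment already exists.

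Two downsides need handling. Section 2.4.1.3 says blinding is removed at the end of treatment, and its wording on what patients learn before and after follow-up is unclear. Week 8 reports may therefore come from unblinded patients and should be read with that in mind. In addition, questions about needle sites could reveal the arm, so the efficacy assessor should not put them before the efficacy ratings are complete.

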4.1 Basic treatment of Parkinson's disease

Both groups will be given basic treatment for PD. Throughout the study, patients in both the MA and SA groups will be required to maintain effective therapeutic doses of anti-Parkinson's drugs at levels like their baseline. Patients with any dosage adjustment, whether an increase, decrease, or adjustment, will be dropped.

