2.4.3.3 Shedding and rejection criteria

A case is considered to be shed if any of the following criteria are met.

(1) Refusal to cooperate with the study arrangements for personal reasons and no longer suitable to continue the study after assessment.

(2) Sudden onset of serious illness, who is assessed to be unfit to continue with the study.

(3) The occurrence of a serious adverse event or an unexpected event.

(4) Those who withdraw from the study on their own.

A case is considered to be rejected if the following conditions are met.

(1) Those who have not completed treatment as required by this study, or the dose or dosing regimen of the anti-Parkinsonian drug need to be adjusted during treatment.

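### Randomised patients with incomplete treatment or an anti-Parkinson dose change are rejected or dropped, which conflicts with the stated intention-to-treat analysis and may end outcome collection that could have continued

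*Protocol*

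**What the plan says.** Two places remove patients after randomisation.

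- Protocol Section 2.4.3.3 lists rejected cases separately from shed cases (withdrawal, serious illness, serious or unexpected events). Rejection covers "Those who have not completed treatment as required by this study" and also cases where "the dose or dosing regimen of the anti-Parkinsonian drug need to be adjusted during treatment".
- Protocol Section 4.1 sets a stable-dose requirement that begins "Throughout the study, patients in both the MA and SA groups will be required to maintain effective therapeutic doses", and then states: "Patients with any dosage adjustment, whether an increase, decrease, or adjustment, will be dropped".

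Protocol Section 5 sets the main analysis: "We used the intention-to-treat (ITT) principle, regardless of whether the patients completed all assigned intervention sessions". On missing values it says: "Multiple interpolation (MI) methods were used to estimate missing data for the primary and secondary outcomes". The one stated check on the imputation is that "sensitivity analyses of the primary outcome were performed using per-protocol (PP) sets". Section 5 does not define the per-protocol set or link it to Section 2.4.3.3 or 4.1.

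In Table S1 the row "Dose of levodopa" is marked at week -1 only. Weekly CSBMs are marked at weeks -1, 0, 1, 2, 3, 4 and 8, and the UPDRS, a secondary outcome, at weeks 0, 4 and 8.

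**The concern.** The rejection rule and the intention-to-treat statement concern the same people: patients who did not finish their sessions. One section removes them and the other keeps them. The dose-change rule adds a second removal for an event after randomisation, which an intention-to-treat analysis does not allow.

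Either event can be related to treatment or outcome. A patient may stop sessions because they are poorly tolerated or bring no benefit. An anti-Parkinson dose may be changed because of motor status, which the trial itself measures with the UPDRS. If such removals differ between arms and are related to bowel outcome, the comparison of weekly CSBMs is biased. This is a risk that the wording creates, not a difference that has been shown.

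The matter belongs in the protocol. Whether diaries and scales are still collected after a dose change or missed sessions is trial conduct. An SAP can define analysis sets, but it cannot recover week-4 or week-8 data that nobody collected.

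**Working it through.** **1. The rules side by side.** Take three randomised patients who are willing to go on completing the diary.

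| Patient | Section 2.4.3.3 | Section 4.1 | Section 5 |
| --- | --- | --- | --- |
| Misses sessions, no dose change | Rejected | Silent | Kept, whatever the sessions completed |
| Dose change in week 2 | Rejected | Dropped | Kept under intention to treat |
| Dose change in week 6 | Not rejected (rule limited to the treatment period) | Dropped (requirement runs for the whole study) | Kept under intention to treat |

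The first row is the plainest conflict. The third shows that the two dose rules disagree with each other in weeks 5 to 8.

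**2. What each reading implies.**

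- Literal: rejected and dropped patients leave the analysis, so it is not intention to treat.
- Milder: dropped means withdrawn and then imputed, and rejected defines the per-protocol set. All randomised patients stay in the main analysis, but later outcomes that could have been observed are replaced by imputed ones. The per-protocol analysis would presumably leave out these same patients, so it could not show whether the imputation was right for them.

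**3. The plan's own figures.** The pilot results in Section 2.4.1.1 give:

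- planned difference = 0.964 − (−0.321) = 1.285 CSBMs per week
- SD = √[(1.726² + 1.310²)/2] = 1.532

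A two-sample t-test at two-sided 5% has power 0.891 with 30 per group and 0.901 with 31, so the stated 31 is reproduced. Allowing for 20% loss, 31/0.8 = 38.75, which rounds up to 39 per group and 78 in total. The sample size is sound, and this point does not affect it.

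**4. Possible bias.** The protocol gives no rate of dose change or rejection, so the fractions below are assumptions. If a fraction f of one arm is removed and those patients would have done D worse than those kept, that arm's mean is shifted by f × D. With D = 1 SD = 1.532 and no recovery by imputation:

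- f = 10% (about 4 of 39): 0.10 × 1.532 = 0.153, and 0.153/1.285 = 12%
- f = 20% (about 8 of 39): 0.20 × 1.532 = 0.306, and 0.306/1.285 = 24%
- D = 0, or the same f and D in both arms: zero bias in the difference

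**5. A second illustration.** Assume no true effect, 39 per arm, no imputation, and removal of the lowest fraction f in one arm on a latent variable whose correlation with outcome is ρ. Then bias = ρ × SD × φ(z_f)/(1 − f). For ρ from 0.3 to 1:

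| f | Bias (CSBMs per week) | Simulated type I error |
| --- | --- | --- |
| 5% | 0.05 to 0.17 | 0.05 to 0.07 |
| 10% | 0.09 to 0.30 | 0.06 to 0.13 |
| 20% | 0.16 to 0.54 | 0.07 to 0.34 |

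At ρ = 0 the bias is zero. The upper ends need removal that is entirely determined by outcome and confined to one arm.

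**The case against.** The strongest defence is that Sections 2.4.3.3 and 4.1 only classify cases, while Section 5 alone sets the efficacy population and names intention to treat, imputation and a per-protocol sensitivity analysis. On that view the sections fit together, and the set definitions and imputation model may be in an SAP that is not shown. The reading is possible, but the protocol does not state it. It would also leave open whether outcome collection goes on, which an SAP cannot settle afterwards.

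A reader might infer more than the text supports. These parts of the objection stand:

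- **That the comparison is certainly no longer between the randomised groups.** This holds only on the literal reading. If dropped patients are imputed, they are still in the randomised groups, and the problem is avoidable missing data.
- **That a dropped patient has no week-4 or week-8 outcome.** No section says that collection stops. A patient dropped in week 6 already has a week-4 value, and earlier weekly CSBMs would usually exist.
- **That imputation treats dropped patients as being like those who stayed.** That depends on the model, which may use earlier weekly CSBMs and is not given.
- **That 20% will be dropped.** The 20% in Section 2.4.1.1 is an allowance for all loss to follow-up.
- **That later dose changes go unrecorded.** Table S1 is not exhaustive: it also omits vital signs and emergency medication, which the text says are recorded. Patients attend 12 sessions in weeks 1 to 4, where a change could be noticed. The gap is clearer in weeks 5 to 8, for which no dose entry is scheduled.

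Patient blinding and a rule worded alike for both arms also lower the risk of uneven removal, without removing it.

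**Conclusion.** The concern holds as a conflict of wording with a practical consequence. Applied as written, the rules in Sections 2.4.3.3 and 4.1 either take randomised patients out of the analysis or may stop their observation for reasons arising after randomisation, against the intention-to-treat statement in Section 5. The periods of the two dose rules also differ and must be reconciled.

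The size of any bias is unknown, and the range starts at zero. The figures of 0.15 to 0.31 CSBMs per week rest on three assumptions from outside the protocol: removal of 10% to 20% in one arm only, a full 1 SD deficit in those removed, and no recovery by imputation. The direction depends on the arm: poor responders lost from the manual acupuncture arm would favour it, and those lost from the sham arm would count against it. The documents do not show that such a bias will occur.

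**What to change.** Amend the protocol to state the following.

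1. A dose change, missed sessions or stopping study treatment does not end outcome collection. Diary and scales continue to week 8 in every randomised patient who has not withdrawn consent.
2. The primary analysis includes all randomised patients with their observed data. Multiple imputation is used only for values that are truly missing, such as those after a patient's own withdrawal.
3. The rejection and dose-change rules in Sections 2.4.3.3 and 4.1 serve only to define the per-protocol set.
4. The period of the dose rule is the same in both sections. Which period it should be is for the investigators to decide.
5. Anti-Parkinson dose is recorded at weeks 4 and 8 in Table S1.

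No change to drug management is implied. The cost is amendment wording, two more dose entries per patient, and continued diary and scale collection in what should be a few patients. The sample size stays at 78.
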